#### Nonresponders

Participants in either group not meeting strict criteria for clinical response^30^ at the 3-month follow-up are offered up to 12 sessions of face-to-face CBT for OCD.^6^ This additional treatment is delivered between the 3-month and 6-month follow-ups. The content of the treatment is identical to the face-to-face CBT treatment, with the main focus on therapist-guided ERP.^28,29^ Individual adaptations are made to ensure optimal treatment dosage, including longer sessions or home visits as appropriate.

#### Therapists

The same therapists treat patients in both groups, and the families have a dedicated therapist throughout the entire treatment. Typically, the assigned therapist is the same clinician who did the baseline clinician assessment. Therapists are clinical psychologists or social workers who specialize in CBT, either experienced in delivery of CBT for pediatric OCD or recently qualified but with training and supervision in the use of the therapy manuals. All therapists have a training session on the treatment manuals and study procedures with the project coordinator prior to starting to support patients. They are closely supervised and monitored by the project coordinator, with weekly meetings throughout the trial, and can also receive on-demand supervision with 12 hours’ notice.

### Outcome Measures

#### Primary Outcome Measure

The primary outcome measure is the participant’s total score on the CY-BOCS,^22^ a semistructured clinician-administered interview for assessment of OCD symptom severity in pediatric OCD. The total score is the sum of 10 items; total scores range from 0 to 40, with higher scores indicating greater severity. The CY-BOCS has a high internal consistency and excellent interrater reliability.^22^ The CY-BOCS is administered at all assessment points. All assessors in the trial receive extensive training in using the CY-BOCS and also practice and rate cases together during the trial on a continuous basis.

#### Secondary Outcome Measures

An overview of the measurements, points for completion, and informant is shown in Table 2. The clinician-rated measures are administered during scheduled assessments at the clinic, and the child- and parent-reported measures are administered online.

**Table 2. zoi190527t2:** List of Measures and Assessment Points

Measure	Assessment Point						
	Baseline	During Treatment	After Treatment	Follow-up			
				3-mo	6-mo	1-y	2- and 5-y
Clinician rated							
MINI-KID	X						
CY-BOCS	X		X	X	X	X	X
CGI-S	X		X	X	X	X	X
CGI-I			X	X	X	X	X
CGAS	X		X	X	X	X	
iiPAS^a^		Week 8	X				
PEAS^b^		Weekly	X				
Child rated							
OCI-CV	X	Weekly	X	X	X	X	
MFQ	X		X	X	X	X	
WSAS-Y	X		X	X	X	X	
CHU9D	X		X	X	X	X	
ISI	X		X	X	X	X	
PEAS		Weekly	X				
WAI		Week 2					
TCES		Week 2					
CSQ			X		X		
Parent rated							
ChOCI-R-P	X	Weekly	X	X	X	X	
FAS-SR	X		X	X	X	X	
MFQ	X		X	X	X	X	
WSAS-P	X		X	X	X	X	
AQ-10	X						
TiC-P	X		X	X	X	X	X
Parent strategies		Weekly	X				
WAI		Week 2					
TCES		Week 2					
CSQ			X		X		

Abbreviations: AQ-10, Autism Spectrum Quotient; CGAS, Children’s Global Assessment Scale; CGI-I, Clinical Global Impression–Improvement; CGI-S, Clinical Global Impression–Severity; ChOCI-R-P, Children's Obsessional Compulsive Inventory Revised-Parent version; CHU9D, Child Health Utility 9D; CSQ, Client Satisfaction Questionnaire; CY-BOCS, Children's Yale-Brown Obsessive Compulsive Scale; FAS-SR, Family Accommodation Scale–Self Rated; iiPAS, Internet Intervention Patient Adherence Scale; ISI, Insomnia Severity Index; MFQ, Mood and Feelings Questionnaire; MINI-KID, Mini International Neuropsychiatric Interview for Children and Adolescents; OCI-CV, Obsessive-Compulsive Inventory–Child Version; PEAS, Patient EX/RP Adherence Scale; TCES, Treatment Credibility and Expectancy Scale; TiC-P, Trimbos/iMTA Questionnaire for Costs Associated With Psychiatric Illness; WAI, Working Alliance Inventory; WSAS-P, Work and Social Adjustment Scale–Parent version; WSAS-Y, Work and Social Adjustment Scale–Youth version.

^a^ Score for iiPAS is measured in the stepped care internet-delivered cognitive behavior therapy group.

^b^ Clinician-rated PEAS is assessed during face-to-face cognitive behavior therapy in the gold standard group.

Secondary clinician-rated outcome measures are the CGI Severity and Improvement scales (CGI-S and CGI-I)^23^ and CGAS.^24^ Severity of OCD symptoms is measured using the child-rated Obsessive-Compulsive Inventory–Child Version (OCI-CV)^31^ and the Children's Obsessional Compulsive Inventory Revised–Parent version (ChOCI-R-P).^32^ Family accommodation behaviors are measured using the Family Accommodation Scale–Self Rated (FAS-SR).^33^ Impairment of functioning due to OCD is assessed using the Work and Social Adjustment Scale–Youth version and Parent version (WSAS-Y and WSAS-P), which are adaptations of the Work and Social Adjustment Scale.^34^ Depressive symptoms are assessed using the short version of the Mood and Feelings Questionnaire (MFQ).^35^ The Insomnia Severity Index (ISI)^36^ is used to quantify the severity of insomnia. The Child Health Utility 9D (CHU9D)^37^ is used as a measure of quality of life and for the estimation of quality-adjusted life years. The Trimbos/iMTA Questionnaire for Costs Associated With Psychiatric Illness (TiC-P),^38^ which measures resource use of health care, social support and assistance, medication use, informal care by parents, and school and work absenteeism over the last 3-month period, is administered to the parents. The Autism Spectrum Quotient (AQ-10)^39^ is used as a baseline measure of autistic symptoms rated by the parent. Other measures are the Treatment Credibility and Expectancy Scale (TCES)^40^ to measure how credible participants perceive the treatment to be, the Working Alliance Inventory (WAI)^41^ to measure working alliance, and the Client Satisfaction Questionnaire (CSQ-8)^42^ to assess participants’ satisfaction with treatment. To measure treatment adherence, the Patient EX/RP Adherence Scale (PEAS)^43^ is used to investigate the amount of exposure and response prevention exercises performed weekly (administered as both a clinician-rated and self-reported measure during face-to-face CBT and as a self-rated version during ICBT), and the clinician-rated Internet Intervention Patient Adherence Scale (iiPAS)^44^ is used only in the ICBT group. To investigate the role of parental behaviors in relation to treatment outcome, questions about parental strategies are administered every week during treatment.

### Safety Procedures

Both children and parents report occurrence of adverse events or undesirable treatment effects in the middle of the course of treatment, after the course of treatment, and at the 6-month follow-up. Adverse events are assessed in the online platform where both the child and the parent report and describe the event and its impact on the child. Reported incidents are categorized depending on severity and frequency in line with GCP. All adverse event assessments will be cross-checked by KTA.

All participants are monitored by the study personnel throughout the study period to ensure participant safety. Therapists and assessors have routines for situations of potential risk. Serious adverse events (ie, events that result in death, suicide attempt, serious violent incident, or admission to the hospital) are documented and monitored by KTA. In case a participant’s condition deteriorates during treatment, the therapist does an immediate in-depth assessment of the symptoms and discusses this with the principal investigator to determine necessary actions. For patient safety reasons, an item to assess suicide risk is added to the child-rated MFQ, which is administered before and after treatment and at 3-month, 6-month, and 1-year follow-ups. If the participant indicates suicidal ideation or has a total score greater than 13 on the child- or parent-rated MFQ (total score ranging from 0-26), the therapist will initiate an assessment of suicide risk.

### Statistical Analysis

#### Baseline Data

Statistical analyses will be conducted under the guidance of the Karolinska Institutet Biostatistics Core Facility. Descriptive statistics with sample characteristics will be presented for each group at baseline. There will not be any formal testing for between-group differences on any baseline variable.^45^ However, we will test for possible site differences at baseline.

#### Outcome Data

The only previous pediatric OCD trial using a noninferiority design used −5 points on the primary outcome measure (CY-BOCS) as a noninferiority margin with an SD of 8.^28^ In the present study, we set the noninferiority margin to −4 points to gain greater precision. The noninferiority analysis will be based on the CY-BOCS score at the primary end point (6-month follow-up) and determined by the confidence interval around the mean difference between the 2 groups. The estimated enrollment is 152 participants, which gives an estimated power greater than 95%, allowing for possible data attrition (10% based on experience from our previous trials). The power is estimated based on each participant being observed at 4 points (baseline, after treatment, 3-month follow-up, and 6-month follow-up). We used a linear random intercept model with 1000 bootstrap samples using the following values, which were based on individual-level data from a previous study of therapist-guided ICBT for adolescents with OCD that used 3 repeated observations^14^: intercept (22.45), slope (−0.37 per week), SD of the random effect (4.03), and SD of the residual error (3.94). In other words, if the stepped care ICBT approach is truly noninferior to the gold-standard treatment, 152 patients will give an estimated probability greater than 95% that the upper limit of a 1-sided 95% confidence interval (or, equivalently, a 90% 2-sided confidence interval) will be below the noninferiority limit of 4 points on the CY-BOCS. No specific noninferiority margin is defined for the secondary outcome measures, but we expect no statistically significant difference between the groups on these measures.

Data will be analyzed according to the participants’ original treatment allocation in line with intention-to-treat principles. Data analysis on the continuous outcome measures will be performed with mixed-effect regression analyses for repeated measures with maximum likelihood estimation. The model will include fixed effects of time, treatment group, and site and an interaction effect of treatment group by time, as well as random intercept and random slope to account for individual differences. In line with our secondary aim, a model with an interaction effect of treatment group, time, and source of referral will be implemented to explore whether source of referral is a moderator of treatment effect. Ordinal data will be analyzed with ordinal regression, binary data will be analyzed with logistic regression, and paired binary data will be analyzed with McNemar tests. Logistic regression will be used to test whether the blinded assessor’s guesses on treatment allocation are better than chance. Within- and between-group effect sizes will be reported as Cohen *d*. If the proportion of missing data is greater than 10%, we will perform multiple imputation with 10 extra data sets.^46^ In a first sensitivity analysis, we will compare the results of the complete-case analysis with those of the multiple-imputed data sets. If the results are inconsistent, we will investigate the reasons of the nonresponse and discuss their possible impact on the study findings. In a second sensitivity analysis, we will exclude the participants who violate protocol (eg, start medication in the middle of the trial) and investigate any inconsistencies with the results from the main analysis. Additional analysis of the 1-year, 2-year, and 5-year follow-up data will evaluate whether the treatment gains are maintained long term.

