Before ICBT for pediatric OCD can be recommended for implementation in routine clinical care, it is essential to evaluate whether this approach is comparable or noninferior and cost-effective compared with the gold standard of face-to-face CBT. Even if ICBT were less efficacious than face-to-face CBT, it might still have a meaningful place in the health system, as its potential cost-effectiveness could outweigh its loss of efficacy. In that scenario, ICBT might be used in a stepped care model in which patients are first offered ICBT as a low-intensity intervention, reserving higher-intensity treatments that require specialist input (eg, face-to-face CBT) for more complex patients or those who do not benefit sufficiently from ICBT.^18^ Stepped care approaches are heralded as the ideal model of psychiatric service delivery^1^ but have rarely been evaluated.

We describe the trial protocol of a multicenter, single-blind, randomized clinical noninferiority trial aimed to investigate whether therapist-guided ICBT implemented within a stepped care model is noninferior to, and cost-effective compared with, the gold standard of face-to-face CBT for pediatric OCD. The main hypothesis is that the stepped care ICBT approach will be noninferior to gold-standard treatment (face-to-face CBT) in reducing clinician-rated OCD symptoms and will also be associated with lower resource use. As a secondary aim, the trial will explore whether the outcomes of ICBT differ between clinic-referred and self-referred patients.

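### The primary model does not adjust for baseline CY-BOCS, so the 6-month difference that decides noninferiority carries part of any chance baseline imbalance and is less precise than it need be

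*Protocol article*

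**What the plan says.** All references are to the protocol article.

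- **Deciding quantity (Outcome Data).** Noninferiority rests on the CY-BOCS at the 6-month follow-up and is "determined by the confidence interval around the mean difference between the 2 groups". The upper one-sided 95% limit "will be below the noninferiority limit of 4 points on the CY-BOCS" if the claim is to succeed.
- **Model (Outcome Data).** "The model will include fixed effects of time, treatment group, and site and an interaction effect of treatment group by time". Each participant is also given a random intercept and a random slope. No baseline CY-BOCS term is listed, and nothing constrains the arms to a common baseline mean.
- **Baseline as an outcome (Outcome Data).** The power calculation has "each participant being observed at 4 points (baseline, after treatment, 3-month follow-up, and 6-month follow-up", so baseline is one of the repeated measurements there.
- **Randomization (Randomization and Allocation Concealment).** Allocation is stratified by referral source and age group, not by baseline severity.

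**The concern.** A treatment main effect beside a treatment-by-time interaction gives each arm its own freely estimated pre-treatment mean. In a randomized trial those means are equal in truth, so any observed gap is chance. The 6-month difference from such a model is the main effect plus the interaction. With time coded as visits and complete data, and leaving the site term aside, it is the raw difference in 6-month means. Neither the stratification nor the listed model terms remove a chance gap in baseline severity from it.

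Two things are at stake. First, noninferiority turns on one confidence limit against 4 points, and that limit is wider than it needs to be. Second, once the baseline table is known, the chance of a false claim is no longer 5%. It is higher if stepped care happened to start with milder cases and lower if it started with more severe ones.

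**Working it through.** **Inputs from the Outcome Data section:** random-intercept SD 4.03, residual SD 3.94, margin 4, one-sided 5%, 152 participants, 10% attrition.

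**Assumptions:** 68 per arm (76 × 0.9 = 68.4, rounded down); normality; assessments at weeks 0, 16, 29 and 42; random-slope SD of 0, 0.10 or 0.15 points per week, since the article gives none; no intercept–slope correlation.

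**1. Spread and correlation (random intercept only).** Total variance = 4.03² + 3.94² = 16.24 + 15.52 = 31.76, so SD = 5.64. Correlation of baseline with 6 months = 16.24 / 31.76 = 0.511.

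**2. The plan's own power figure.** Unadjusted SE = 5.636 × √(2/68) = 0.967. Power at a true difference of 0 = Φ(4/0.967 − 1.645) = 99.4%. This agrees with the stated figure of above 95%.

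**3. Size of chance imbalance.** The baseline difference between arms also has SE 0.967, about a quarter of the margin. Each point of imbalance moves the unadjusted 6-month contrast by 0.51 points with time as visits, or by 0.41 with linear time.

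**4. Precision after adjustment.** SE = 0.967 × √(1 − 0.511²) = 0.831. The variance reduction is 0.511² = 26%.

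**5. Power at a true difference of 2 points.**
- Unadjusted: Φ(2/0.967 − 1.645) = 66%.
- Adjusted: Φ(2/0.831 − 1.645) = 78%.

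**6. With the planned random slope (time as visits).** The 6-month variance is 31.76 + (42 × slope SD)². The correlation is 16.24 / √(31.76 × 6-month variance).

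| Slope SD (per week) | 6-month variance | Correlation | SE unadjusted | SE adjusted | Variance reduction |
|---|---|---|---|---|---|
| 0 | 31.76 | 0.51 | 0.967 | 0.831 | 26% |
| 0.10 | 49.40 | 0.41 | 1.205 | 1.099 | 17% |
| 0.15 | 71.45 | 0.34 | 1.450 | 1.363 | 12% |

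With linear time the SE goes from 0.886 to 0.777 at slope SD 0 (23% less variance) and from 1.142 to 1.060 at 0.10 (14%). If the correlation were 0.3 or 0.2, the reduction would be 0.3² = 9% or 0.2² = 4%.

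**7. Conditional false-claim rate at a true difference of 4 (time as visits, random intercept only).** The claim is made when the estimate falls below 4 − 1.645 × 0.967 = 4 − 1.590. An imbalance of 1 SE shifts the estimate by 0.511 × 0.967 = 0.494, and the remaining SD is 0.831.
- Stepped care starts 1 SE lower: Φ((−1.590 + 0.494)/0.831) = 9.4%.
- Stepped care starts 1 SE higher: Φ((−1.590 − 0.494)/0.831) = 0.6%.
- Baseline-adjusted contrast: 5% in both cases.

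At correlation 0.3 the first figure is 7.9%.

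**The case against.** The strongest reply is that nothing here is invalid. Averaged over randomizations, the unadjusted contrast has 5% one-sided error. The 9.4% is conditional on an imbalance in one direction and is offset by 0.6% in the other, as with any unadjusted randomized comparison. The power statement holds without adjustment, and the 66% v 78% comparison is at a true difference of 2 points, for which the trial was not sized. All of this stands, and it makes the point one of efficiency and conditional validity.

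The 26% gain also belongs to a random-intercept model, whereas the analysis model adds a random slope. That stands too, and the smaller range is the fairer one. The entry rule of CY-BOCS 16 or more may narrow the baseline spread, and hence the imbalance, further.

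It can be said that detail may sit in the full protocol in the Supplement, which is not shown. Time coding may well be there and is not criticized. But the article lists the fixed effects itself, and the point concerns that list. Baseline's place in the outcome vector is inferred from the power paragraph. If baseline is not in it, the listed terms contain no baseline adjustment at all and the imbalance still enters.

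A reader might go further and infer that the plan offers two rival deciding contrasts. The Introduction's hypothesis is to be "noninferior to gold-standard treatment (face-to-face CBT) in reducing clinician-rated OCD symptoms", and the group-by-time term estimates a difference in change. Picking whichever succeeds would inflate the error rate. The document does not support this reading. Outcome Data names the difference in 6-month score as the deciding quantity and never says that the interaction decides noninferiority. In a model that includes baseline, the interaction is needed simply to obtain the 6-month difference. Inflation would require a departure from the plan.

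**Conclusion.** The point holds as a worthwhile improvement to a stated model, not as an error of validity. The listed primary model leaves baseline CY-BOCS unadjusted, so the deciding difference absorbs roughly 0.4 to 0.5 points per point of chance baseline imbalance and loses precision.

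The variance that could be saved is 26% with a random intercept only and time as visits. It is about 12% to 17% with a random slope of assumed SD 0.10 to 0.15, and about 4% if the baseline to 6-month correlation is as low as 0.2. The gain matters little if the arms are truly equal, where unadjusted power is already 99.4% on the plan's inputs. It matters more if stepped care is somewhat worse but within the margin, a possibility the Introduction itself raises for ICBT. Neither an inflated unconditional error rate nor a wrong power figure follows from this.

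**What to change.** In Outcome Data, change the primary CY-BOCS model in one of two ways:

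- constrain the baseline mean to be equal in both arms, by dropping the treatment main effect at baseline and keeping time and treatment by time; or
- model only the post-baseline visits, with baseline CY-BOCS as a covariate.

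The two give close but not identical results under linear time, random slopes or dropout, so one should be chosen and stated.

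Then tie the decision to the model: the noninferiority contrast is this model's baseline-adjusted difference (stepped care minus gold standard) at the 6-month follow-up, with its upper one-sided 95% limit compared with +4. Use the same form for the continuous secondary measures that have a baseline.

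The cost is one or two sentences. No new data or patients are needed, because the CY-BOCS is already taken at baseline (Table 2). The change should be made before any between-group outcome comparison is seen.

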## Introduction

Cognitive behavior therapy (CBT) is regarded as the gold-standard treatment for pediatric obsessive-compulsive disorder (OCD)^1,2^ and has consistently shown large effect sizes compared with both wait-list (*g* = 1.53) and various active comparators (*g* = 0.93)^3^ as well as sustained long-term effects.^4^ Furthermore, CBT is an effective augmentation treatment for patients showing suboptimal response to initial courses of both serotonin reuptake inhibitors^5^ and CBT.^6^ Unfortunately, suitably trained CBT therapists specializing in OCD are scarce and typically concentrated in large urban areas, and it is estimated that many patients do not have access to CBT.^7,8,9,10^ One way to increase the availability of CBT is to remotely deliver it online without the need to attend in-clinic sessions with a therapist.^11^ Our research group has developed a therapist-guided internet-delivered CBT (ICBT) program for youth with OCD called *BIP OCD*. The treatment is primarily self-guided, with assistance from parents or legal guardians, and supported by a designated therapist who communicates with both the child and the parent through the entire treatment. The BIP OCD program has to date been evaluated in 2 open pilot studies in both children^12^ and adolescents^13^ that showed high acceptability and safety and promising results. A subsequent randomized clinical trial including 67 patients demonstrated superiority and cost-effectiveness of BIP OCD against a wait-list control.^14,15^ Interestingly, the effects of ICBT were slightly weaker than expected but continued beyond the primary end point, with patients experiencing additional symptom improvement at the 3-month follow-up. This delayed improvement phenomenon has also been observed in other ICBT trials.^16,17^ As participants in these trials were primarily self-referred^12,13,14^ and may therefore constitute a selected group of individuals (eg, highly educated, more motivated), the generalizability of these findings to regular clinic-referred patients is currently unclear.

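### The coding of fixed time in the primary model is not stated; if it is linear, as in the power model, the 6-month contrast is biased whenever the between-group gap is not linear in time

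*Protocol article*

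**What the plan says.** All references are to the Protocol article.

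- **Target.** Outcome Data: "The noninferiority analysis will be based on the CY-BOCS score at the primary end point (6-month follow-up"), judged by the confidence interval for the mean difference between groups against a 4-point limit.
- **Analysis model.** Outcome Data: "mixed-effect regression analyses for repeated measures with maximum likelihood estimation", with fixed effects of time, group and site, and "an interaction effect of treatment group by time, as well as random intercept and random slope to account for individual differences". Whether fixed time is linear, piecewise or categorical is not stated.
- **Power model.** Outcome Data: "We used a linear random intercept model with 1000 bootstrap samples", with "intercept (22.45), slope (−0.37 per week), SD of the random effect (4.03), and SD of the residual error (3.94"), each participant being "observed at 4 points (baseline, after treatment, 3-month follow-up, and 6-month follow-up"). This is the only place where a form for time is given.
- **Expected course.** The Introduction reports that the effects of ICBT continued after treatment in the earlier trial, "with patients experiencing additional symptom improvement at the 3-month follow-up". Nonresponders says of the further face-to-face CBT: "This additional treatment is delivered between the 3-month and 6-month follow-ups".

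**The concern.** A random slope needs continuous time, at least in the random part. Read together with the per-week slope in the power model, the natural (though not explicit) reading is that fixed time is linear too. The 6-month difference would then be the gap between two straight lines evaluated at 6 months, not the gap between the observed 6-month means. Visits before the step-up would help to determine it.

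That matters because the strategy under test acts late. ICBT may work more slowly and keep improving, and further CBT is offered only in the last interval. If the gap opens early and closes late, a straight-line contrast carries the early gap into the 6-month estimate. A stepped-care arm that had caught up could then fail the noninferiority test. As written, the text allows two analyses that could reach opposite conclusions on the sole primary question.

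**Working it through.** **Inputs.** From Outcome Data: random-effect SD 4.03, residual SD 3.94, margin 4, one-sided 5% (z = 1.645), 152 participants, 10% attrition. From Study Design: 16 weeks of first treatment, primary end point 6 months later. Assumptions: visits at weeks 0, 16, 29 and 42; complete data on 68 per arm (76 × 0.9 = 68.4).

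**1. The plan's own figure.** For a single 6-month visit, variance = 4.03² + 3.94² = 31.76 (SD 5.64). SE = √(2 × 31.76/68) = 0.967. Power = Φ(4/0.967 − 1.645) = 0.994; with 76 per arm it is 0.997. For the linear random-intercept model it is 0.998 and 0.999. The stated power above 95% is reproduced either way.

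**2. Coefficients under linear fixed time.** The mean week is 21.75 and the sum of squared deviations is 968.75. The coefficient for the visit at week t is 1/4 + (42 − 21.75)(t − 21.75)/968.75:

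- week 0: 0.25 − 0.455 = −0.205
- week 16: 0.25 − 0.120 = 0.130
- week 29: 0.25 + 0.152 = 0.402
- week 42: 0.25 + 0.423 = 0.673

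They are the same with or without a random slope. The 6-month coefficient is 0.66 with months 0, 4, 7 and 10, 0.70 with visit number, and 0.77 if baseline means are constrained equal. With categorical fixed time it is 1 and the others are 0.

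**3. When this biases the result.** If both arms follow the same curve, it cancels and the bias is 0. If the difference grows linearly from 0 to 4, the estimate is 4.0, which is correct. Bias needs a between-group difference that is not linear in time.

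**4. A gap that narrows late.** Illustrative differences 0, 4, 3.5, 0.5: estimate = 0.130 × 4 + 0.402 × 3.5 + 0.673 × 0.5 = 2.26, against a true 0.5.

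- *Stated SDs, no slope variance.* Linear model: variance = 4.03² + 0.673 × 3.94² = 26.69, SE = 0.886, P(noninferior) = Φ((4 − 2.26)/0.886 − 1.645) = 0.62. Baseline-adjusted 6-month contrast: variance = 31.76 − 16.24²/31.76 = 23.46, SE = 0.831, P = Φ(3.5/0.831 − 1.645) = 0.99. Without baseline adjustment (SE 0.967), P = 0.98.
- *Assumed slope SD 0.10 per week.* This adds (42 × 0.10)² = 17.64 to each variance. Linear: SE = √(2 × 44.33/68) = 1.142, P = 0.45. Baseline-adjusted: SE = √(2 × 41.10/68) = 1.100, P = 0.94. Unadjusted: SE = √(2 × 49.40/68) = 1.205, P = 0.90.

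**5. Other shapes at a true 6-month difference of 4.**

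- 0, 4, 4, 4: estimate 4.82, and noninferiority is declared about 1% of the time, below the nominal 5%.
- 0, 0, 0, 4: estimate 2.69, and it is declared 43%, 31% or 26% of the time at slope SDs of 0, 0.10 and 0.135.

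**The case against.** The strongest objection is that the article never says fixed time is linear. Categorical fixed time with a random slope is a legitimate model and fits the text. The word linear belongs to the power model, which already differs from the analysis model by having no random slope. The article also points to a full protocol in a Supplement that is not shown, where the coding may be given. This stands, so linearity is an inference. What remains is that the article does set out its primary model, and the only form of time it offers does not match its stated target.

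Several stronger readings are tempting and are not supported:

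- *The random slope causes the problem.* It does not; the coefficients are the same without it.
- *Curved trajectories are enough.* They are not. The 16-week course, the pause and the further CBT for nonresponders apply to both arms, and curvature shared by both arms cancels.
- *Only 67% of the information comes from month 6.* The 0.67 is a coefficient in a set that sums to 1 and includes a negative baseline term. It is not a share.
- *Type I error is out of control.* The profile 0, 0, 0, 4 produces this, but it needs stepped care to fall behind only in the interval when its nonresponders are offered face-to-face CBT. The documents' own mechanisms point the other way.
- *The power-model slope implies a mean of 22.45 − 0.37 × 42 = 6.9 at the end point.* That is true, but a mean common to both arms cancels in the difference.

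**Conclusion.** The point holds conditionally. If fixed time is linear, the model does not estimate the 6-month difference that the decision is tied to, except when the between-group difference is linear in time. For a gap that narrows late, which the Introduction and the Nonresponders section make plausible, it overstates the inferiority of stepped care and loses power. In the example the estimate is 1.8 points too high, and the chance of showing noninferiority falls from about 0.99 to 0.62 on the stated SDs, or from 0.94 to 0.45 at a slope SD of 0.10. False noninferiority needs a gap that widens late, which is less expected here.

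The coefficients depend only on visit timing and change little across reasonable codings. The difference profiles and the slope SD are assumptions, so the probabilities show possible size and do not predict the result. If categorical time is already intended, one sentence settles the matter.

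**What to change.** State in the primary model that fixed time is a categorical visit factor (baseline, post-treatment, 3-month, 6-month) with group-by-visit terms, and that the two-sided 90% CI for noninferiority is taken from the 6-month visit contrast. The random effects can stay as planned. A linear model may be kept as descriptive. Adjusting for baseline and reporting the 3-month contrast from the same model are optional extras.

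The cost is a change of wording before the 6-month data are analysed, two more time parameters per arm, and a small loss of precision: on the stated SDs, SE 0.967 against 0.886 at 68 per arm. Power at no true difference is still 99.4%. At the assumed slope SD of 0.10 it is Φ(4/1.205 − 1.645) = 0.953 without baseline adjustment and Φ(4/1.100 − 1.645) = 0.977 with it, against Φ(4/1.142 − 1.645) = 0.968 for the linear model. No new data are needed.
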